### Data analysis

#### Missing data and data treatment

We aim for including as many data as possible from participants who meet the eligibility criteria. In general, we intend to exclude participants only when necessary for the given analysis. Because this is a mechanistic study [28] and we intend to use latent-variable modeling, we plan to conduct per-protocol analysis. Therefore, for analyses beyond pretest data, we intend to include only participants who have completed at least one posttest session and 70% of training sessions. We will not impute any data.

We will apply transformations to this data as needed (e.g., *z*-transformations) based on the properties of the collected data (e.g., non-normal distribution). Such transformations and the reason for performing the transformations will be documented and reported. We intend to operationalize task performance in the training tasks using the drift rate. If using the drift rate is not possible because the data properties prevent us from fitting diffusion models, we will use mean RTs, switching and dual tasking costs. In addition, we will analyze training effects on the other parameters of the drift diffusion model, in particular boundary separation and non-decision time, and test how changes in these parameters relate to changes in the transfer tasks.

#### Computational and statistical modeling

We will estimate the diffusion model parameters for performance in the training tasks. Simulation studies have shown that the EZ/Robust EZ diffusion model [87, 88] is adequate for a wide range of applications [89]. Indeed, the Robust EZ model [88] was suitable for a preliminary analysis of choice RT data from a previous study [39]. However, depending on the properties of the acquired data set, we may need to use other diffusion model implementations with different estimation procedures such as the hierarchical diffusion model [90]. The parameters of the diffusion model that are directly relevant to our main hypotheses are drift rate, response caution, and non-decision time.

We plan to use latent change-score models to evaluate training and transfer gains, modeled after those previously reported by Schmiedek et al. [91]. To compare latent change between the different conditions, we will run these models for multiple groups simultaneously. We will first test all four levels of measurement invariance (configural, metric, scalar, and strict invariance) across study sites, times, and groups. Next, we will test whether latent change differs between two conditions by comparing model fit when this parameter is allowed to vary freely or is fixed to be the same between groups.

If the models fail to converge, we will use Bayesian linear-mixed effects modeling to account for variance from multiple individuals and tasks following the same procedures as in our previous work [5, 6]. More specifically, if using linear mixed-effects models, we would include fixed effects of group (4 training conditions) and age (continuous variable from 18 to 85 years), and random effects of participant (individual ID) and task (e.g., drawings, numbers, shapes for the training tasks).

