### Objectives

The overarching goal of this study is to identify the cognitive processes improved by training speed tasks and how they are affected by varying attentional control demands across the adult lifespan. This study goes beyond previous cognitive training studies by using diffusion modeling to estimate theoretically and psychologically meaningful components of information processing and relating them to gains in untrained contexts. For this purpose, we pursue the following objectives:Examine how extensive speed training affects the cognitive processes involved as reflected by changes in diffusion model parameters, and whether these changes in cognitive processes vary across the lifespan.Investigate how changes observed in these cognitive processes are related to transfer effects in working memory, inhibitory control, reasoning, and everyday cognitive functioning, and whether these changes are maintained after the end of the training intervention.Determine how attentional control demands of training interventions modulate these effects.

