### Design

Table 1 provides an overview of the study design. This multi-site, longitudinal, double-blinded, and actively controlled study uses a mixed 4 (training condition, between-subjects: simple RT, choice RT, task switching, and dual task training) × 3 (time, within-subjects: pretest, posttest, follow-up) factors design with age as covariate.

**Table 1 Tab1:** Schedule of enrollment, assessments, and interventions

Measure	Study phase and timepoint									
	Pre-assessment	Pretest				Intervention	Posttest		Follow-Up	
	T0–P	T0–Q	T1–V1	T1–V2	T1–R	S1–S10	T2–V1	T2–V2	T3–V1	T3–V2
*Enrolment*										
Eligibility screening and conditional enrolment	X									
Informed consent^a^		X	X							
MoCA assessment, confirmation of eligibility, and final enrolment			X							
Randomization					X					
*Interventions*										
Active control: Simple RT						X				
Experimental—low: Choice RT						X				
Experimental—medium: Switching						X				
Experimental—high: Dual tasking						X				
*Assessment of Training and Near Transfer Gains*										
Simple RT tasks (drawings, shapes, numbers)				X				X		X
Choice RT tasks (drawings, shapes, numbers)				X				X		X
Switching tasks (drawings, shapes, numbers)				X				X		X
Dual tasks (drawings, shapes, numbers)				X				X		X
*Assessment of Far Transfer Gains*										
Working memory										
Updating			X				X		X	
Binding			X				X		X	
Continuous reproduction			X				X		X	
Inhibitory control										
Go/no-go			X				X		X	
Number stroop			X				X		X	
Simon			X				X		X	
Reasoning										
Matrix reasoning			X				X		X	
Paper folding			X				X		X	
Letter sets			X				X		X	
Everyday cognitive functioning										
Cognitive Failures Questionnaire (CFQ)			X				X		X	
Questionnaire d’Auto-évaluation de la Mémoire (QAM)			X				X		X	
Everyday Problems Test (EPT)			X				X		X	
*Assessment of Individual Characteristics*										
Socioeconomic background		X								
Cognitive training experience and motivation		X								
Computer and internet literacy		X								
Self-rated physical health		X								
General self-rated health			X				X		X	
Depression, Anxiety and Stress Scale—21 Items (DASS-21)		X								
Activities of Daily Living-Prevention Instrument (ADL-PI)			X				X		X	
Leisure activities		X								
Active driving		X								
Big Five Inventory (BFI)		X								
Short Grit Scale (Grit-S)		X								
Theories of Intelligence Scale (TIS)			X				X		X	
Exercise Self-Efficacy Scale (EXSE)		X								
General Self-Efficacy Scale (GSE)			X				X		X	

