#### Sample size

We aim for a total sample size of at least 400 participants (*n* = 100 per condition) recruited across the three sites. To account for stratification (see below), our goal is to recruit *n* = 136 participants per site (*N* = 408). Based on previous cognitive training studies, training effects tend to be very large, whereas transfer effects tend to be small. The required sample size to achieve 80% power at α = 0.05 for a small effect size (Cohen’s *f* = 0.10) is *N* = 280 for a main effect of condition on change in transfer measures from pretest to posttest. However, in this study, an additional aim is to determine how changes in cognitive processes during training (i.e., the diffusion model parameters) relate to changes in the transfer measures using multi-group latent-change score models, a structural-equation modeling technique. Currently, no empirical simulation studies exist offering guidelines for optimal sample sizes [32]. We therefore estimated the required sample size based on previous studies using similar techniques [33, 34] and general power considerations for correlational designs. According to simulation studies [35], correlations of *r* = 0.24, as are typically found for the relationship between processing speed and fluid intelligence [11], tend to stabilize at sample sizes between *N* = 304 to *N* = 341 (90% power, corridor of stability w = 0.10). The total sample size of *N* = 408 participants will allow for some attrition (~15 to 20%).

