### Randomization

After the two pretest sessions and before the first training session, participants will be randomly assigned to one of the four conditions. The study will be conducted double blinded, that is, neither participants nor assessors will be aware of group affiliation.

Before the start of recruitment, a stratified list of group assignments is randomly generated centrally at the Sheffield site by an unblinded research team member, using the *sample()* function in R. To ensure an even distribution of the four groups, the list is generated in blocks of four group assignments at a time. Following this pre-generated list, participants within each stratum (age and gender) who completed the second pretest session will be randomly allocated to one of the four groups for each study site separately to maximize equal distribution of these characteristics in each training condition and study site. For stratification purposes only, we will form age groups that are about equally distributed across age decades:Ages 18–29 years: 24 participantsAges 30–39, 40–49, 50–59, and 60–69 years: 20 participants eachAges 70–85 years: 32 participants

Participants who completed both pretest sessions and were allocated a training condition but have not yet started their training intervention, as evidenced by not having opened the training tasks, will be replaced by new participants until the desired sample size is reached.

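### The latent-change models name no age, gender or site predictor and no age-by-condition test, although age is the design's covariate, lifespan variation is part of Objective 1, and randomisation is stratified by all three factors

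*Protocol article*

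**What the plan says.** All of this is in the protocol article.

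- **Design:** a four-condition by three-time "factors design with age as covariate".
- **Objectives:** the first objective includes "whether these changes in cognitive processes vary across the lifespan".
- **Randomization:** "participants within each stratum (age and gender) who completed the second pretest session will be randomly allocated to one of the four groups". This is done separately at each of the three sites, in blocks of four, using six age bands.
- **Computational and statistical modeling:** "To compare latent change between the different conditions, we will run these models for multiple groups simultaneously". The test compares model fit with the change parameter free or held equal between two conditions. Site appears only as one of the groupings for measurement-invariance testing.
- **The same section, if the latent models do not converge:** "we would include fixed effects of group (4 training conditions) and age (continuous variable from 18 to 85 years", with random effects for participant and task. Gender, site and a group-by-age term are not listed.
- **Hypotheses 1 to 5 (analysis sections):** each compares latent change, or its relation to transfer, between conditions. None mentions age, gender or site.

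**The concern.** The design and objectives give age a role that the stated models do not carry out. The consequences differ by use:

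1. **Objective 1.** The main models have no age term, so following the plan yields no answer on whether change varies over the lifespan. The fallback's age main effect could at most show whether gain depends on age overall, and only if the outcome is a gain score. It cannot show whether this differs by training condition.
2. **Hypotheses 1 to 4.** Stratification balances age, gender and site across arms. If these factors predict change, leaving them out keeps their variance in the error term, so standard errors are too large and the test is conservative. The Sample size section itself expects small transfer effects.
3. **Hypothesis 5.** Regressing transfer change on drift-rate change is, within a condition, a non-randomised association. The Background says that fluid abilities decline with age and that diffusion parameters are sensitive to age differences. Over 18 to 85 years, age could drive both changes.

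**Working it through.** **1. The plan's own figure.** The Sample size section gives N = 280: "The required sample size to achieve 80% power at α = 0.05 for a small effect size" (f = 0.10), "for a main effect of condition on change in transfer measures from pretest to posttest". The pre-post correlation is not stated; ρ = 0.5 is assumed. For a group-by-time test with 4 groups and m = 2 times:

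- noncentrality λ = f² × N × m / (1 − ρ) = 0.01 × 280 × 2 / 0.5 = 11.2
- degrees of freedom 3 and 276
- power 0.806

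The smallest equal-group N reaching 80% is 280, so the figure reproduces. No covariate enters it, so the stated N does not depend on adjustment.

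**2. Analysable number per arm.** Strata per site: 24 + 4 × 20 + 32 = 136, and 3 × 136 = 408. With the plan's upper attrition of 20%, 408 × 0.80 = 326.4, or about 82 per arm.

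**3. True alpha when balanced stratifiers are left out.** Let R² be the share of change variance explained by age, gender and site. The documents give no value, so a range is assumed. Under balance the estimate's variance shrinks by (1 − R²), but the unadjusted standard error does not. True alpha = 2 × [1 − Φ(1.96 / √(1 − R²))].

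| R² | 1.96 / √(1 − R²) | True alpha |
|---|---|---|
| 0.05 | 2.011 | 0.044 |
| 0.10 | 2.066 | 0.039 |
| 0.20 | 2.191 | 0.028 |
| 0.30 | 2.343 | 0.019 |

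**4. Power for one pairwise comparison.** The difference of 0.3 SD of change is illustrative and not taken from the plan. Normal approximation, n = 82 per arm: power = Φ(0.3 × √(n/2) / √(1 − R²) − 1.96), where 0.3 × √41 = 1.921.

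- Unadjusted: Φ(1.921 − 1.96) = 0.48
- Adjusted, R² = 0.10: Φ(2.025 − 1.96) = 0.53
- Adjusted, R² = 0.20: Φ(2.148 − 1.96) = 0.57

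Allowing for the balance in the unadjusted test changes little: Φ(−0.039 / √0.8) = Φ(−0.044), still 0.48.

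**5. The overall condition test at N = 326.** On the scale of step 1, power is 0.867 unadjusted, 0.903 at R² = 0.10 and 0.936 at R² = 0.20. The overall test is therefore comfortable. The loss falls on the pairwise comparisons, which are what the hypotheses use.

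**6. Objective 1 and Hypothesis 5.** No arithmetic applies. Set side by side, the Design section and Objective 1 require age in the analysis of change, and the analysis sections for Hypotheses 1 to 5 contain no age term.

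**The case against.** **An article may leave covariates to a fuller plan.** A preregistration exists and is not shown. For gender and site this carries weight, since their absence is only silence. For age it does not suffice: the article states the covariate role and the lifespan question, sets out its models hypothesis by hypothesis, and names age only in the fallback.

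**The fallback list may not be exhaustive.** It names no time term and refers to the team's previous procedures, so a missing group-by-age term is weak evidence that none is planned. This stands as a caution.

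**Change scores already remove stable level differences.** This is true. Age, gender and site leave removable variance only if they predict change, and the documents do not show that they do. Hence R² is an assumed range.

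**Pretest.** A reader might infer that the models make no pretest adjustment and that adding it would be worth 11 to 33% more participants. The documents do not support this. A latent-change model contains the pretest factor by construction; whether change is regressed on it or merely covaries with it is not stated. With equal pre and post variances, the variance ratio of conditioned to raw change is (1 − r²) / [2(1 − r)] = (1 + r)/2, which is 0.75 at r = 0.5, 0.90 at r = 0.8 and 0.95 at r = 0.9. The gain thus runs from 33% (1/0.75) down to about 5% (1/0.95), rests on a correlation the plan does not give, and is nil if the planned model already conditions on pretest.

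**Conclusion.** The point holds for age and, less strongly, for gender and site. The plan should be changed, but it is not broken.

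- **Objective 1:** as written, its age question has no test in the main models.
- **Hypothesis 5:** the association is open to confounding by age. Whether confounding occurs depends on age predicting both changes, which is plausible but not shown.
- **Precision:** at an assumed R² of 0.10 to 0.20, true alpha is about 0.039 to 0.028, and power for a 0.3 SD pairwise difference is 0.48 unadjusted against 0.53 to 0.57 adjusted, with about 82 per arm.

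A reader might also infer that the treatment comparison is biased or that N = 280 is wrong. Neither follows. Omitting stratifiers does not bias the randomised contrast, and the sample-size figure reproduces without covariates. One qualification: the analysis set is per-protocol (at least one posttest session and 70% of training sessions), so the balance given by stratification is not guaranteed there, and adjustment guards against this only in part.

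**What to change.** - In each latent-change model, including those for Hypothesis 5, regress latent change on continuous age, gender and two site indicators. Centre these on the whole sample, so that the change parameter compared between conditions refers to an average participant.
- For Objective 1, report the age slope on latent change and test it as free versus equal across conditions.
- In the fallback mixed model, add gender, site and condition-by-age.
- State that latent change is regressed on latent pretest. This is safer than constraining pretest means to be equal across conditions: exclusions after randomisation mean equality is not guaranteed in the per-protocol set, and a false constraint would shift the estimated difference in change.

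These variables are already collected, so data collection does not change. The cost is a few more parameters per group in multi-group models with about 82 participants per arm, where the plan already provides for non-convergence. The order in which covariates would be dropped if a model fails should therefore be stated in advance.

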### Hypotheses

#### Hypothesis 1

(training gains): On average, participants in the three experimental conditions will show larger pre-post improvements in their respective training tasks than participants in the active control condition.

#### Hypothesis 2

(near transfer gains): On average, participants in the three experimental training conditions will show larger pre-post improvements in the untrained processing speed training tasks of the other experimental conditions than participants in the active control condition.

#### Hypothesis 3

(far transfer gains): On average, participants in the three experimental training conditions will show larger pre-post improvements in working memory, inhibitory control, reasoning, and everyday cognitive functioning than participants in the active control condition.

#### Hypothesis 4

(attentional control demands): Compared to the active control condition, experimental training conditions with stronger attentional control demands will induce larger near and far transfer effects. Specifically, transfer effects will be largest after dual task training, followed by switching training, and, lastly, choice RT training.

#### Hypothesis 5

(underlying mechanism): Training-induced changes in drift rate in the experimental training conditions relative to the active control condition predict the size of near and far transfer effects, and the relationship between training-induced change in drift rate and the size of transfer effects will be stronger with increased attentional control demands of the training condition. Specifically, we expect this relationship to be strongest after dual task training, followed by switching training, and, lastly, choice RT training.

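### The fallback mixed model for Hypotheses 1 to 4 lists only group and age as fixed effects and names no outcome, so its group term may not be the difference in change, and it has no group-by-age term for Objective 1

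*Protocol article*

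**What the plan says.** The Design section sets out four training conditions crossed with "3 (time, within-subjects: pretest, posttest, follow-up) factors design with age as covariate". The hypotheses are worded as differences in change. Hypothesis 3, for example, expects that trained participants "will show larger pre-post improvements in working memory, inhibitory control, reasoning, and everyday cognitive functioning than participants in the active control condition". The first objective also asks "whether these changes in cognitive processes vary across the lifespan".

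The primary analysis matches this: "We plan to use latent change-score models to evaluate training and transfer gains". The section on Hypothesis 1 applies it to three contrasts: pretest to posttest, pretest to follow-up, and posttest to follow-up.

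The fallback is in Computational and statistical modeling: "If the models fail to converge, we will use Bayesian linear-mixed effects modeling to account for variance from multiple individuals and tasks". The sentence refers to procedures in the team's earlier studies, and the next one lists the terms: "we would include fixed effects of group (4 training conditions) and age (continuous variable from 18 to 85 years", together with "random effects of participant (individual ID) and task (e.g., drawings, numbers, shapes for the training tasks". No dependent variable is named. Time, group × time, pretest score and group × age are not listed.

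**The concern.** The list keeps condition and age from the design and drops time, the factor through which Hypotheses 1 to 4 are defined. The article did not leave this model to another document; it gave the terms one by one, and an analyst would implement that list.

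Because the outcome is not named, the list fits at least three models: all scores pooled over occasions, posttest scores alone, or gain scores. They differ in what the group coefficient estimates and how precisely. The choice between them would be made after the primary models had failed on the collected data, which is the freedom that preregistration is meant to remove.

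The per-protocol rule adds to this. Analyses beyond pretest keep only participants with at least one posttest session and 70% of training sessions. After that selection, randomization alone no longer guarantees balanced pretest scores, and a model that mixes levels with change is exposed to any imbalance.

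**Working it through.** **Inputs.** From the Sample size section: N = 280, f = 0.10, α = 0.05, 80% power, four equal groups, effect of condition on change from pretest to posttest. Assumption: pre-post correlation ρ = 0.5, with 0.7 as a variant, because the document gives none. Scores are scaled to SD 1 at each visit after age adjustment.

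**1. Reproduce the plan's figure.** For the group × time interaction with four groups and two visits, the noncentrality is λ = f² × N × 2/(1 − ρ) = 0.01 × 280 × 2/0.5 = 11.2 on 3 and 276 degrees of freedom. Power is 0.806, and 280 is the smallest N in equal groups that reaches 80%. With two visits this is the same test as a group effect on change scores. The trial was therefore sized for a difference in change.

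**2. What the group term estimates.** Let b be the baseline difference between two groups and d the difference in gain.

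- Two visits pooled: [b + (b + d)]/2 = b + d/2.
- Three visits pooled, effect fully maintained: [b + (b + d) + (b + d)]/3 = b + 2d/3.
- Posttest only: b + d.
- Gain score: (b + d) − b = d.
- Posttest adjusted for pretest: d, when b is a chance imbalance.

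**3. Precision.** In step 1, f = 0.10 means that the group gains have an SD of 0.20 between groups. For each model, λ = N × (SD of the group effects)² / (variance of the outcome per person).

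| Model | Variance | λ at ρ = 0.5 | Simulated power, ρ = 0.5 | Simulated power, ρ = 0.7 |
|---|---|---|---|---|
| Two visits pooled, no time term | (1 + ρ)/2 = 0.75 | 280 × 0.10²/0.75 = 3.73 | 0.34 | 0.30 |
| Posttest only | 1 | 280 × 0.20²/1 = 11.2 | 0.80 | 0.80 |
| Gain score | 2(1 − ρ) = 1 | 280 × 0.20²/1 = 11.2 | 0.80 | 0.97 |
| Posttest adjusted for pretest | 1 − ρ² = 0.75 | 280 × 0.20²/0.75 = 14.93 | 0.92 | 0.98 |

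The simulations used 3,000 runs with age as a covariate. The noncentral F values at ρ = 0.5 (0.33, 0.81, 0.81 and 0.91) agree.

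For three visits pooled with a maintained effect and equal correlations, the effect SD is 0.20 × 2/3 = 0.133 and the variance is (1 + 2ρ)/3 = 0.667. Then λ = 280 × 0.133²/0.667 = 7.47, and power is about 0.61.

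The variance of the pretest-adjusted comparison relative to the gain comparison is (1 − ρ²)/[2(1 − ρ)] = (1 + ρ)/2. This is 0.75 at ρ = 0.5 and 0.85 at ρ = 0.7, so the benefit of adjustment shrinks as the correlation rises.

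**4. Age.** With age as a main effect only, a gain-score model estimates one age slope common to all four groups, including controls. That slope mixes retest gains with training gains. Whether training-induced change varies with age is the group × age term, or age × group × time in the occasion form.

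**The case against.** The strongest reply is that the outcome is meant to be a gain score. The Sample size section describes the powered effect as a main effect of condition on change, the models being replaced evaluate gains, and Hypothesis 1 is analysed contrast by contrast. One gain model per contrast, with group and age fixed and participant and task random, would be coherent, and its group term would be the group difference in gain. The cited earlier work, which is not at hand, may say exactly this. This reply stands in part. A reader might infer from the list that the fallback is unable to test Hypotheses 1 to 4, or that most of the power is lost. The document does not support that, because both statements need a raw-score outcome pooled over visits, which it never states. Equally, it never states the gain-score outcome for this model.

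Three further points hold. An unadjusted gain comparison is valid under randomization, so the missing pretest term costs precision and is not an error. The five hypotheses contain no age hypothesis, and the sections on them spell out no age term for the latent models, so the age gap is not peculiar to the fallback. The planned inference uses Bayes factors, with values between 0.33 and 3 treated as ambiguous, so power at a 5% test describes relative precision and not the planned decision rule.

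A condensed article may leave detail elsewhere. Here, however, it chose to list the terms, and the list as given leaves the estimand open.

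**Conclusion.** The point holds as a fault of specification in a named contingency analysis, limited to Hypotheses 1 to 4.

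- **Scores pooled over occasions:** the group term is not the difference in change. It carries half of it over two visits, or two-thirds over three visits with a maintained effect, plus any baseline difference.
- **Gain scores:** the test is valid but less precise than a pretest-adjusted one. Simulated power is about 0.80 against 0.92 at ρ = 0.5, and 0.97 against 0.98 at ρ = 0.7.
- **Either reading:** there is no term for the age question in Objective 1.

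The power figures rest on N = 280 and f = 0.10 from the protocol, on the assumed correlation, and on a frequentist test used only as a guide. Hypothesis 5 is not covered, because its section gives a separate course if the multigroup models do not converge. A reader might suppose that non-convergence is likely and that this model will become the main analysis; nothing in the document allows that to be judged.

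**What to change.** Name the dependent variable of the fallback and state one of two forms:

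1. Posttest (or follow-up) score on pretest score, group, age and group × age, with random participant and task effects. The Bayes factor for the group term tests Hypotheses 1 to 4. Age should be centred so that this term refers to a stated age.
2. Score by occasion on group, time, group × time and age, plus age × group × time with its lower-order terms, and the same random effects. The Bayes factor for group × time is the test.

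The first form gains the precision of pretest adjustment. The second also gives the posttest-to-follow-up contrast directly. If gain scores are what is intended, the text should say so and add group × age.

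The cost is one or two sentences of analysis wording. All the variables are already collected, and the sample size does not change.
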